## **8. Examination and evaluation**

### **(1) Participant background**

Subject identification code, initial, gender, date of birth, date of hospital admission, race, height at admission, weight at admission, BMI at admission, vital signs at admission (blood pressure, pulse rate, temperature), comorbidities, past medical history, smoking status, history of falls within 3 months prior to enrollment, level of care required, prescription drug information, laboratory results at admission (serum creatinine level, serum sodium level, serum potassium level, eGFR, pO2, pCO2), current medical history (name of diagnosis) will be obtained at the time of enrollment.

### **(2) Intervention Items**

Allocation group.

### **(3) Endpoints**

#### **<Primary endpoints>**

All-cause deaths, unscheduled visits, and rehospitalizations up to 12 months after allocation will be confirmed

by telephone survey every 2 months, including specific dates, referring to the entries in the follow-up diary provided in advance. A hospital transfer is considered to be a continued hospitalization, and a rehospitalization is defined as "hospitalization due to any new event". If necessary, we will request information from the patient's primary care institution, primary care pharmacy, home nursing station, after making a request for research cooperation in advance.

### **<Secondary endpoints>**

After 6 months and 12 months of enrollment, the researcher or research collaborator will contact the participant via telephone and interview about the following information. If it is deemed difficult to interview the participants themselves, a NoK will be asked the same information. Information on medications will be recorded at the time of enrollment and hospital discharge, and inquiries will be made by telephone or fax to the community pharmacy at 6 months and 12 months.

1. Symptoms: To be confirmed by interview.
2. Adverse events: Detailed of events, date of onset/disappearance, degree, treatment required, outcome, severity assessment, and relevance to the intervention will be reported using case report form according to CTCAE version 5.0.
3. Number of medications: Descriptive statistics of the number of medications taken at admission, discharge, and 6 and 12 months after study enrollment and the proportion of drug names.
4. Number of potentially inappropriate prescriptions: Descriptive statistics of the number of potentially inappropriate prescriptions and the proportion of potentially inappropriate drug names. Potentially inappropriate prescriptions are defined as medications that meet STOPP criteria version 2.
5. Health-related quality of life: Measured at baseline, 6 months, and 12 months using the EQ-5D Japanese version. At baseline, a face-to-face survey will be conducted by the researcher, and thereafter, interviews will be conducted via telephone.
6. Level of long-term care required: To be ascertained by interviewing the patient or NoK.
7. Falls and injuries due to falls

**Table. Timetable of the MPEG trial**

|                                                                                    | Baseline
assessm
e n t | Enrollm
e n t | Follow-
u p 1 | Follow-
u p 2 | Follow-
u p 3 | Follow-
u p 4 | Follow-
u p 5 | Follow-
u p 6 |
|------------------------------------------------------------------------------------|------------------------------|------------------|------------------|------------------|------------------|------------------|------------------|------------------|
| Time point (week)                                                           | 0                            | 0                | 8 ± 2            | 16 ± 2           | 24 ± 2           | 32 ± 2           | 40 ± 2           | 48 ± 2           |
| Enrollment                                                                  |                              |                  |                  |                  |                  |                  |                  |                  |
| Informed consent                                                                   | x                            |                  |                  |                  |                  |                  |                  |                  |
| Sociodemographic
characteristics                                                | x                            |                  |                  |                  |                  |                  |                  |                  |
| Allocation                                                                         |                              | x                |                  |                  |                  |                  |                  |                  |
| Intervention                                                                |                              | x                |                  |                  |                  |                  |                  |                  |
| Assessments                                                                 |                              |                  |                  |                  |                  |                  |                  |                  |
| Subjective
symptoms                                                             | x                            | x                | x                | x                | x                | x                | x                | x                |
| Adverse events                                                                     |                              |                  | x                | x                | x                | x                | x                | x                |
| Vital signs                                                                        | x                            |                  |                  |                  |                  |                  |                  |                  |
| Height and weight                                                                  | x                            |                  |                  |                  |                  |                  |                  |                  |
| Unscheduled visits                                                                 |                              |                  | x                | x                | x                | x                | x                | x                |
| Hospital
readmission                                                            |                              |                  | x                | x                | x                | x                | x                | x                |
| Injury due to falls                                                                |                              |                  | x                | x                | x                | x                | x                | x                |
| Laboratory tests
(eGFR, serum
sodium level, and
serum potassium
level) | x                            |                  |                  |                  |                  |                  |                  |                  |
| Number of
prescribed
medications                                             | x                            |                  |                  |                  | x                |                  |                  | x                |

|                                                             |   |   |  |  |   |  |  |   |
|-------------------------------------------------------------|---|---|--|--|---|--|--|---|
| Number of prescribed potentially inappropriate medications* | x |   |  |  | x |  |  | x |
| EQ5D-3L                                                     |   | x |  |  | x |  |  | x |
| Level of long-term care required                            | x |   |  |  | x |  |  | x |

\*The number of prescribed potentially inappropriate medications listed in the STOPP/START criteria version 2.

## 9. Criteria for study discontinuation

- (1) When a subject declines to participate in the study or withdraws consent
- (2) When eligibility is found to be unmet after enrollment
- (3) When it is difficult to continue the study due to exacerbation of complications
- (4) When adverse events make it difficult to continue the study
- (5) When the entire study is terminated
- (6) The investigator deems it appropriate to terminate the study for other reasons.

If the investigator determines that the study cannot be continued for one or more of the above reasons, the intervention will be stopped immediately and the date of discontinuation or dropout, reason for discontinuation or dropout, and progress will be noted in the medical record, and necessary tests will be performed at the time of discontinuation or dropout to evaluate efficacy and safety. If the intervention is discontinued due to an adverse event, the patient should be followed up as much as possible until the patient recovers to the original condition.

## 10. Handling of adverse events

### (1) Treatment of participants with adverse events

The medication adjustment proposal in the intervention group in this study is not mandatory, and actual prescription decision and follow-up will be made at the discretion of the attending physician. Therefore, the risk of adverse events in the intervention group is not expected to deviate significantly from usual care.

However, in the unlikely event of an adverse event associated with the intervention, the principal investigator or study personnel will take appropriate action immediately.

## **( 2 ) Reporting of serious adverse events**

Serious adverse events in this study are defined as follows.

- 1) Death or threat of death
- 2) Hospitalization or prolonged hospitalization
- 3) Disability or risk leading to disability
- 4) Acquired or congenital disease or abnormality

All serious adverse events during the study period will be reported by the principal investigator to the president (Chairman of the Institutional Ethical Committee).

## **11. Reporting deviations from the protocol**

The investigator or principal investigator may deviate from or change the study protocol for compelling reasons, such as emergency avoidance, before obtaining prior approval from the President (Institutional Ethical Committee). In such cases, the investigator or principal investigator shall record all details and reasons for the deviation or change, and if a revision of the study protocol is necessary, the proposed revision will be promptly submitted to the Institutional Ethical Committee for deliberation and approval by the President.

## **12. Termination, Discontinuation or Suspension of the Study**

### **(1) Termination of the study**

At the end of the study, the principal investigator shall promptly submit a study termination report to the President.

### **(2) Discontinuation or interruption of the study**

The principal investigator will consider whether or not to continue the study in the following cases

1. When it is judged to be difficult to achieve the planned number of enrollment due to difficulties in recruitment.
2. When the Institutional Ethical Committee requests changes in the protocol, and it is judged to be difficult to accept such changes.
3. When the Institutional Ethical Committee recommends or instructs to discontinue the study, the study will be terminated.

When a decision is made to discontinue or suspend a study, the decision will be promptly reported in writing

to the President, together with the reason for the discontinuance or suspension.

### **13. Duration of the study**

The enrollment period for the study is planned to be 3 years and 3 months from the Institutional Ethical Committee approval, but may be extended or terminated earlier depending on the status of enrollment. The follow-up period for each subject will be one year.

### **14. Data aggregation and statistical analysis methods**

Data will be stored in eACReSS, and data will be compiled after data cleaning by the data center prior to statistical analysis.

#### **(1) Analysis set**

The analysis of the primary and secondary endpoints will include all study participants enrolled in the study. If it is found that the eligibility criteria are not met after the start of the study, they will be excluded from the analysis. The analysis of the safety endpoints will be performed on all participants enrolled in the study.

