## 6. Study methods

### ( 1 ) Design

Single-center open-label prospective randomized controlled trial

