### ( 4 ) Intervention

The prescription optimization scheme for the intervention group is shown in Figure 2. For subjects assigned to the intervention group after consent is obtained, the prescription optimization support team collects and reviews information and proposes a prescription adjustment plan to the team in charge within 2 days of assignment. Specifically, drug names, blood test data, disease names, etc. are entered into the computerized prescription optimization support system, and the system automatically creates a prescription optimization draft based on STOPP/START. The Prescribing Optimization Support Team, consisting of a physician, pharmacist, and nurse, then conducts a drug review of the subject based on the Prescribing Optimization Protocol (Figure 3) and develops a Prescribing Adjustment Plan. Prescription suggestions (addition, reduction,

discontinuation, etc.), their rationale, and precautions after prescription changes are documented and provided in writing to the physician in charge, leaving the final prescription details to the judgment of the physician in charge. After a change in prescription, if the ward nurse, pharmacist, or physician in charge provides information on any changes that may be related to the prescription, the Prescribing Optimization Support Team will respond as appropriate. At the time of discharge, the Prescription Optimization Support Team will prepare a drug information report after confirming the participant's condition, and provide it to the primary care physician.

Figure 2.

[figure not shown]

Figure 3.

[figure not shown]

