#### **(2) Statistical analysis methods**

Participants who can no longer be contacted during the follow-up will be treated as censored when they were last contacted. Discontinuation of the study participation will not be considered a termination, thus observation will continue.

For the primary endpoint analysis, a survival function will be estimated for each group using the Kaplan-Meier method, which will be used to estimate survival rates and 95% confidence intervals at 6 and 12 months. Group comparisons will be made using stratified log-rank tests (two-sided) with stratified age groups (65-74, 75-84, 85+) as the strata. The significance level is set at 0.05. The baseline hazard will be stratified based on age group strata, and the hazard ratio and its 95% confidence interval will be calculated for the intervention group compared to the usual care using a Cox regression model with the time until rehospitalization, unscheduled hospital visit, or all-cause death as the outcome variable and the allocation group as the explanatory variable.

The same analysis as above will be performed for each of the time to rehospitalization, unscheduled visits, and all-cause mortality, which comprise the primary composite endpoint. The planned statistical tests are unadjusted for the multiplicity.

Subgroup analysis of the primary endpoint will be performed for each index disease (heart failure, pneumonia, diabetes, stroke, urinary tract infection) and drug class (antiplatelet/anticoagulant,

antihypertensive, antidiabetics, sedatives). The 12-month survival rate will be estimated for each subgroup by group and evaluated to see if the difference between groups is in the same direction as the overall analysis.

Details of the analysis methods for secondary endpoints and safety endpoints will be defined in a separate statistical analysis plan.

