## **15. Sample size calculation and its rationale**

Based on previous studies, we estimate the event rate at 12 months for the primary endpoint to be 30% for the intervention group and 40% for the control group. Assuming equally spaced enrollment and allocation, a total of 423 subjects would be needed for the analysis to have a power of 0.80 with a two-sided test at a significance level of 0.05. We estimate 15-20% exclusion from the analysis and plan to enroll a total of 500 subjects (250 in each group) over the 2-year period.

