## **16. Consideration for human rights, safety and disadvantage of study participants**

Candidates for study participation will be provided with sufficient information prior to study enrollment, and only those who have given written consent to participate will be included in the study. We plan to fully explain that: participation in the study is voluntary and not compulsory; no disadvantage will be incurred if consent is not given; consent can be withdrawn at any time even if requested; in such cases, the clinical information collected will be destroyed and not used for research; data is personal information and will be strictly managed; and the data will be kept in a locked cabinet, separated from personal identifying information (e.g. name, date of birth, patient ID). Personal information including test values will be anonymized so that individuals cannot be identified. Anonymized information collected in this study may be used for secondary analyses in the future with the approval of the Institutional Ethical Committee, and this will be clearly stated and fully explained in the explanation and consent document.

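### Participants found ineligible after randomisation are dropped from the efficacy analyses of an open-label trial, with no safeguard on that judgement and no all-randomised analysis

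*Combined protocol and SAP*

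**What the plan says.** Protocol section 14(1) and SAP section 3 both take all enrolled participants as the set for the primary and secondary endpoints, then add the exception "If it is found that the eligibility criteria are not met after the start of the study, they will be excluded from the analysis". For safety, protocol section 14(1) makes no such exception: "The analysis of the safety endpoints will be performed on all participants enrolled in the study".

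The design is given in protocol section 6(1) as "Single-center open-label prospective randomized controlled trial". Under protocol section 6(4), within 2 days of assignment and in the intervention arm, "drug names, blood test data, disease names, etc. are entered into the computerized prescription optimization support system", and the team then reviews the patient's drugs.

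Protocol section 9 lists as a reason for discontinuation "When eligibility is found to be unmet after enrollment". Section 14(2) states "Discontinuation of the study participation will not be considered a termination, thus observation will continue". For participants who withdraw consent, section 16 states "in such cases, the clinical information collected will be destroyed and not used for research".

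The only figure for losses is in protocol section 15, repeated in SAP section 2.2: "We estimate 15-20% exclusion from the analysis". Neither place gives reasons or a split by arm.

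**The concern.** Removing people after randomisation is harmless only if the removals are unrelated to arm, or unrelated to prognosis. Here neither condition is protected. Staff know the allocation, there is no deadline for finding someone ineligible, and the judgement could be made after an outcome is known.

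There is also a specific route to imbalance. A structured review of the drug list after allocation takes place in one arm only, and the drug count is an entry criterion. A patient whose true count is below five is more likely to be noticed where a team goes through the list line by line.

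At stake is who enters the primary log-rank test and the Cox model. With no all-randomised analysis planned even as a sensitivity analysis, a reader could not see whether the exclusions mattered. The safety set adds an oddity: SAP sections 10.5 to 10.8 tabulate primary-endpoint events under safety, where everyone is kept. The same events could thus be counted in the safety tables and left out of the efficacy result.

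**Working it through.** **The plan's own figure.** Section 15 needs 423 for analysis and enrols 500. 423/(1 − 0.15) = 498 and 423/(1 − 0.20) = 529, so 500 matches the 15% end. Losses of 15-20% from 500 are 75-100 people. This is a total for all causes. It gives neither the number found ineligible nor the split by arm, so it cannot be used as an input for the bias.

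**Inputs.** From the documents: 40% control event rate at 12 months, 250 per arm, two-sided 0.05, 12 months of follow-up each. Assumed, because the documents give no figure: the fraction x removed from the intervention arm, and the 12-month event risk q of those removed. No true effect is assumed, so the true rate is 40% in both arms.

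**Formulae.**
- Observed intervention rate: p₁ = (0.40 − x·q)/(1 − x)
- Apparent hazard ratio: HR = ln(1 − p₁)/ln(1 − p₀), with p₀ the control rate
- Events: d = n₁p₁ + n₀p₀; share of patients in the intervention arm: a = n₁/(n₁ + n₀)
- Drift of the log-rank statistic: m = √(d·a·(1 − a))·ln HR
- Two-sided rejection probability: Φ(−1.96 − m) + 1 − Φ(1.96 − m)

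This is the Schoenfeld normal approximation. It ignores the age stratification.

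**One case in full: x = 10%, q = 80%.** 25 of 250 are removed, 20 of them with events.
- p₁ = (0.40 − 0.08)/0.90 = 0.356
- HR = ln(0.644)/ln(0.60) = 0.86
- d = 225 × 0.356 + 250 × 0.40 = 180; a = 225/475 = 0.474
- m = √(180 × 0.474 × 0.526) × ln(0.86) = 6.70 × (−0.151) = −1.01
- Rejection probability = Φ(−0.95) + 1 − Φ(2.97) = 0.172

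**Range.**

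| Removed, intervention | Their risk | Removed, control | Observed rates | HR | Type I error |
|---|---|---|---|---|---|
| 2% | 60% | 0 | 39.6% v 40% | 0.99 | 0.051 |
| 5% | 40% | 0 | 40.0% v 40% | 1.00 | 0.050 |
| 5% | 60% | 0 | 38.9% v 40% | 0.97 | 0.057 |
| 5% | 80% | 0 | 37.9% v 40% | 0.93 | 0.077 |
| 10% | 20% | 0 | 42.2% v 40% | 1.07 | 0.079 |
| 10% | 60% | 0 | 37.8% v 40% | 0.93 | 0.079 |
| 10% | 80% | 0 | 35.6% v 40% | 0.86 | 0.172 |
| 15% | 60% | 0 | 36.5% v 40% | 0.89 | 0.124 |
| 10% | 80% | 5% at 80% | 35.6% v 37.9% | 0.92 | 0.082 |
| 17.5% | 60% | 17.5% at 60% | 35.8% v 35.8% | 1.00 | 0.050 |

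Bias needs exclusions that differ by arm and are related to prognosis. If either is absent, it vanishes. If those removed are at low risk, it runs against the intervention.

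**The case against.** The strongest reply is that late ineligibility may be rare and even-handed. Protocol section 8(1) collects prescription, laboratory and diagnosis data at enrolment in both arms. Section 6(5) returns an eligibility confirmation at registration for every participant. Data cleaning and central monitoring are not arm-specific. A reader might infer that the control arm is never checked and that failures will be found mainly in the intervention arm. The documents do not support that. The asymmetry is one additional review, which supports saying that failures could be found more often there, and no more.

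Most entry criteria are also poorly suited to being overturned later. Expected stay, fitness for oral drugs and life expectancy are the attending physician's judgements at entry, and an early death or short stay does not in itself show that they were wrong. Illustrations built on removing patients with short life expectancy therefore fit the mechanism badly. The criterion clearly exposed is the drug count, and the documents give no event risk for patients who fail it.

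The SAP has partial safeguards: a flow diagram that counts ineligible and discontinued cases (6.1) and a list of discontinuations with reasons (6.2). Neither is explicitly by arm, and neither changes who is analysed.

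On withdrawn consent, section 16 can be read as a specific rule that overrides the general one in section 14(2). That reading is coherent. But section 9 lists withdrawal of consent among the discontinuations, so the text still leaves both rules applying to the same person.

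What stands after all this is that the exclusion rule has no safeguard and no all-randomised analysis accompanies it.

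**Conclusion.** The point holds as a weakness in the definition of the analysis set. It is not a demonstration that the result is biased. Size and direction are unknown from the documents. On the assumptions above (no true effect, normal approximation), bias is nil when exclusions are balanced in number and risk or are of average risk. With exclusions in one arm only, it is small at 2-5% with moderately raised risk (type I error 0.051 to 0.057 at 60% risk). It becomes material at about 10%, or when those removed differ strongly in prognosis.

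Two further inferences should be resisted. One is that the 15-20% in section 15 measures ineligibility: no cause is given, so it may cover any loss. The other is that keeping everyone would restore power by raising the analysed number to 500. That would treat all the expected losses as recoverable by this change, which the documents do not say.

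The question of data after withdrawal of consent is a separate matter of wording to be reconciled. No mechanism specific to one arm is evident for it.

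**What to change.** In protocol section 14(1) and SAP section 3:

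- Define the primary efficacy set as all randomised participants, analysed in the arm to which they were allocated, whether or not ineligibility is found later.
- Keep the present set as a sensitivity analysis only. Ineligibility should be judged on data that predate allocation, by someone unaware of arm and outcome.
- In SAP sections 6.1 and 6.2, report exclusions and withdrawals by arm and reason.

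Separately, reconcile protocol sections 9, 14(2) and 16 on whether data are kept or destroyed when consent is withdrawn. This must stay within the commitments given to participants: destruction is something they are told, so retention cannot simply be imposed, and data already destroyed cannot be recovered.

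The cost is mainly wording. Participants found ineligible should still have outcome data, because section 9 treats them as discontinued and section 14(2) continues observation. The statistical price is slight dilution of the effect from a few ineligible patients. The SAP revision history shows that version 1.2 was written after an analysis had been run, so an all-randomised analysis added now should be labelled as such, with the pre-specified set shown beside it.
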